### Data Collection Methods

All assessors are trained to conduct the assessments for children with and without CP. Outcome data will be collected at assessments.

The Dyskinesia Impairment Scale measures the severity of dystonia and choreoathetosis when an individual is at rest or conducting movement. It was found to show good to excellent reliability and validity [27]. It is also notable that in a 2012 systematic review of measures of dystonia and choreoathetosis, this scale is listed as the only clinical tool that examines choreoathetosis and dystonia in the same scale [28].

The Selective Control of the Upper Extremity Scale is a video-based tool to measure selective control of upper limb tasks. Psychometric analysis shows “comparable validity to other accepted video-based clinical assessment tools for the upper extremity in children with CP” with content validity ratio values indicating substantial agreement for most items [29].

The Quality of Upper Extremity Skills Test is 36 items in length and measures upper limb movement, hand function, and cooperativeness in children with CP. It has been found to be reliable to assess children with CP in the age range of 18 months and 8 years, with increased reliability in children aged up to 12 years [30]. It has also been found to show adequate to excellent validity [31,32].

The Tardieu scale examines spasticity with quantified measures of the responses to stretch reflexes of discrete velocity. This scale shows high test retest and poor to moderate inter-rater reliability; the Tardieu scale performs better than other similar measures, however, indicating it may be more reliable [33].

The Montreal Spasticity Rating Test is a quantitative measure of spasticity that identifies resistance to external forces of stretch tasks. This test identifies the point at which the stretch reflex is activated in a muscle. Documentation on the reliability and validity of this test is unavailable.

The WHODAS II-CY is a self-administered 36-item document that assesses daily issues surrounding health conditions such as illnesses, injuries, and problems with mental health. In a validity study, it was found to show good reliability; however, limitations regarding options for those without significant disabilities were present [34].

Plans to promote participant retention include payment at the end of, or separation from, the study.

### Data Management

All data will be deidentified. Paper medical records will be brought by participants to the testing site or sent by US mail to the principal investigator’s university address; they will be stored under double lock. All consent and assent forms will be completed at a testing site. Clinical test results performed during the experiment will be paper-recorded, and deidentified data will be inputted electronically for data analysis. Input of electronic records will be verified by 2 different members of the research team. Tests that record data electronically, such as sEMG, will be kept electronically. Data collected from source documents will be inputted into an encrypted and password-protected computer that is secured by the campus firewalls.

Paper records will be locked in a double-locked cabinet. All electronic data will be stored on password-protected computer that is secured by the campus firewalls. The computer designated for data collection and experimentation will not be connected to the internet for heightened security. All deidentified data will be submitted to an online repository as required for publication of randomized clinical trials.

### Statistical Methods

The assessment and training protocols target improvements in selective motor control and amelioration of dystonia. We will conduct paired *t* tests on movement primary and secondary outcomes for the CP and TD groups independently. In case of non-normality, nonparametric techniques will be used. Differences before and after as well as before and follow-up will be obtained on the primary outcome measure: smoothness of movement. Tests on secondary outcomes are for exploratory purposes only. Bonferroni corrections will be applied as needed.

Missing values will be omitted from calculations or corrected for according to standard statistical techniques.

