**Conclusions:**

Movement outcomes will be examined for changes in muscle activation and clinical measures in children with dystonic CP and TD children. Paired *t* tests will be conducted on movement outcomes for both groups of children independently. Positive and negative results will be reported and addressed.

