### Choice of Comparator

Children aged 7 to 17 years with dystonic CP and a group of typically developing (TD) children in the same age range will be recruited for the study. The CP and TD groups will be randomly assigned to an intervention or no-intervention (control) group. The control groups will be assessed in the same schedule as the intervention groups. Participants will continue with their regular PT schedule and continue their typical exercise regimen as applicable.

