### Trial Design

We will conduct paired *t* tests on movement outcomes for the CP and TD groups independently. In case of non-normality, nonparametric techniques will be used. Differences before and after as well as before and follow-up will be obtained on the primary outcome measure: smoothness of movement. Differences will also be calculated on secondary outcomes for exploratory purposes. The primary outcome measure will be the smoothness index of the accelerometry signals of sensors placed on the upper limb segments. Secondary outcomes include the interaction force with the robot and a battery of clinical tests and a quantitative measure of spasticity. The study is powered for the main outcome. The desired allocation will be 1:1, with 1 participant in the control group for every participant in the intervention group for both CP and TD participants.

In the application presented here, the VR environment follows a prescribed remapping based on principal component analysis of force data generated from people with typical movement control [22,23]. Participants will, therefore, be asked to produce efforts in directions of high variance that are associated with performance of typically developed adults.

This intervention will not be incorporated into a broader health care program at this time.

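### The stated analysis is a before-after paired t test within the CP and TD groups; the randomised intervention and control arms are never compared

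*Protocol article*

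**What the plan says.** Under Choice of Comparator the protocol article states: "The CP and TD groups will be randomly assigned to an intervention or no-intervention (control) group". It adds: "The control groups will be assessed in the same schedule as the intervention groups". Trial Design and Table 5 give 1:1 allocation, with 17 children in each of the four cells. The Objective section asks for the effect of the training on movement outcomes in children with dystonic CP.

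The analysis is described three times:

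- Statistical Methods: paired t "tests on movement primary and secondary outcomes for the CP and TD groups independently".
- Trial Design: paired t "tests on movement outcomes for the CP and TD groups independently".
- Abstract, Conclusions: paired t "tests will be conducted on movement outcomes for both groups of children independently".

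Statistical Methods defines what is differenced: "Differences before and after as well as before and follow-up will be obtained on the primary outcome measure: smoothness of movement". The fallback is: "In case of non-normality, nonparametric techniques will be used". Bonferroni correction is to be applied where needed. Allocated arm appears in none of these statements. The Sample Size section works from a within-subject effect size, dz = 2.98.

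**The concern.** A randomised trial estimates a treatment effect by comparing the arms. The analysis here compares each child with his or her own baseline, and the groups it keeps apart are the diagnostic groups, CP and TD, not the randomised arms.

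The wording allows two readings. Literally, trained and untrained children with CP are pooled in one paired test. More generously, a separate paired test is run in each arm. Neither estimates the difference between arms.

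Change within an arm can arise without any training effect. The primary outcome comes from a movement task repeated at each visit, usual physical therapy continues, and the Limitations section accepts that participants cannot be blinded. A control arm on the same schedule removes change common to both arms, but only if the arms are compared. Without that comparison, a significant before-after change could be read as a training effect even if controls improved equally. Noting that the change is significant in one arm and not in the other is not a valid substitute.

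**Working it through.** **Inputs from the protocol article.** Sample Size: dz = 2.98, alpha 0.05, power 0.8, required n = 4 per comparison group; 17 per cell, 68 in total; 25% attrition, leaving about 13 per group. Sidedness is not stated; two-sided is assumed.

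**Step 1: reproduce the protocol's own figure.** The power of a paired t test comes from the noncentral t distribution with df = n − 1 and noncentrality dz·√n.

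- n = 3: noncentrality 2.98 × √3 = 5.16, power 0.741.
- n = 4: noncentrality 2.98 × √4 = 5.96, power 0.965.

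The smallest n with power of at least 0.80 is 4, as stated. Attrition also agrees: 17 × 0.75 = 12.75, about 13, and 4 × 17 = 68. A two-sample test with d = 2.98 would also give 4 per group (power 0.777 at 3, 0.936 at 4), so n = 4 alone does not settle which test was planned. The protocol's own label of the effect size as within-subject does.

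**Step 2: how the stated test behaves when training has no effect.** Let every child, in either arm, change by a common amount c, in units of the SD of change. The values of c are assumptions; the protocol gives none. Let p be the rejection probability of the paired test with 13 children (df 12, noncentrality c·√13). Because the arms are independent, the chance that the intervention arm is significant and the control arm is not equals p(1 − p). The pooled test uses 26 children.

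| Common change c | Intervention arm significant, n = 13 (p) | Significant in intervention only, p(1 − p) | CP arms pooled, n = 26 |
|---|---|---|---|
| 0.3 | 17% | 14% | 31% |
| 0.5 | 38% | 24% | 69% |
| 0.8 | 75% | 19% | 97% |
| 1.0 | 91% | 8% | 99.8% |

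For example, at c = 0.5 the noncentrality is 0.5 × √13 = 1.80, p = 0.382, and p(1 − p) = 0.382 × 0.618 = 0.236. A valid two-sided 5% comparison of the arms would reject in 5% of such trials, 2.5% of them in favour of the intervention.

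**Step 3: pooling when training does work.** If only trained children improve, by d = 0.8 SD, the mean change over 26 pooled children is 0.4 SD. The pooled SD is about √(1 + 0.8²/4) = 1.077, so dz is about 0.4/1.077 = 0.37 and power is about 44%. The pooled estimate is half the true effect.

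**Step 4: what a between-arm test can detect.** For a two-sample t test on change in the CP stratum, df = 2n − 2 and noncentrality is d·√(n/2).

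- Detectable difference at 80% power: 1.15 SD with 13 per arm; 0.99 SD with 17 per arm.
- With alpha halved to 0.025 for two time points: 1.28 SD and 1.10 SD.
- Power with 13 per arm: 11% at 0.3 SD, 23% at 0.5, 50% at 0.8, 69% at 1.0, 84% at 1.2. This range is assumed, because the protocol gives no between-arm effect size.

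**The case against.** The design itself is sound on this point: allocation is concealed, the ratio is 1:1, and controls are measured on the same schedule. The data can therefore answer the question, and only the stated analysis cannot. That is correct and sets the limit of the criticism.

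It may be said that an article condenses a fuller plan that could contain the contrast between arms. That does not rescue the text. The article names its test three times, defines the differences as before-after and before-follow-up, and sizes the study on a within-subject effect. This is a stated choice, not an omitted detail.

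The Sample Size section also calls this a pilot-phase trial. However, the Objective is to establish an effect, and Trial Design says the study is powered for its main outcome.

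Three further cautions stand. The common-change values are assumptions. Regression to the mean is a weak argument here, since no eligibility criterion selects on baseline smoothness. Lost power is not the main harm of pooling: about 44% pooled against 50% for an unadjusted between-arm test at 0.8 SD is a small gap. The harm is that a change is attributed to training without a comparison that supports it.

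**Conclusion.** The point holds: the analysis is wrong as written and must be changed. No stated test uses the randomisation, and neither reading of the paired tests isolates the training effect. If training has no effect but both arms share a change of 0.3 to 0.8 SD, a nominal 5% paired test is significant in 17% to 75% of trials within the intervention arm, and in 31% to 97% with arms pooled. Inferring an effect from significance in the intervention arm alone is wrong in 14% to 24% of trials over the same range. The size depends on how large the shared change is, which the protocol does not say. The absence of a comparison between arms does not depend on that assumption.

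**What to change.** Make the primary analysis the intervention-minus-control difference in post-training smoothness among all randomised children with CP, analysed as randomised, by ANCOVA adjusted for baseline smoothness, with a 95% confidence interval. A baseline-constrained mixed model over the three visits is an acceptable alternative. A two-sample test of change scores would also be valid but less precise: the ANCOVA-to-change variance ratio is (1 − r²)/(2(1 − r)) = (1 + r)/2, which is 0.75 at a baseline-to-post correlation r of 0.5 and 0.85 at 0.7 (assumed values).

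Run the same contrast separately in TD children as exploratory, and present within-arm changes as descriptive only. Adjusting for age, and replacing the normality-triggered switch of test with a pre-stated permutation test of the same contrast, are useful but optional.

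Amend Statistical Methods, Trial Design and the Abstract together. Restate the Sample Size rationale on a between-arm effect and report what 13 completers per arm can detect: about 1.15 SD of change before any gain from baseline adjustment.

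The cost is rewording. No new measurements are needed, and no new participants if that sensitivity is accepted. The article says the trial has not started, so the change can be made before any data exist.

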### Sample Size

No previous sample data exist for this type of study that would enable sample size calculations. Data from a study on finger muscle control in children with dystonic CP with a mean difference effect size for within-subjects designs of dz=2.98, alpha=.05, and power=0.8 yields a required sample size of n=4 in each comparison group [26]. Given the wide age range and motor impairment characteristics in the eligibility criteria for this study, we propose a sample size of n=17 with a total number of 68 participants. We expect a 25% attrition rate that will approximately yield a total of 13 participants per group. We consider that this number is a conservative estimate for a randomized controlled trial in the pilot phase.

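### The primary smoothness test may switch after a normality check on about 13 children per group; if paired differences are skewed, the switch does not restore the 5% level, and one fixed between-arm test would

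*Protocol article*

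**What the plan says.** The Statistical Methods section states "We will conduct paired *t* tests on movement primary and secondary outcomes for the CP and TD groups independently" and continues "In case of non-normality, nonparametric techniques will be used". Trial Design repeats the rule: "tests on movement outcomes for the CP and TD groups independently. In case of non-normality, nonparametric techniques will be used".

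For the primary outcome the rule applies to two contrasts: "Differences before and after as well as before and follow-up will be obtained on the primary outcome measure: smoothness of movement". With CP and TD analysed separately, that makes at least four separate choices of test.

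Sample Size gives the numbers on which normality would be judged: "we propose a sample size of n=17 with a total number of 68 participants", and then "We expect a 25% attrition rate that will approximately yield a total of 13 participants per group". Trial Design also provides randomised controls in each population: "The desired allocation will be 1:1, with 1 participant in the control group for every participant in the intervention group".

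The article does not say whether each paired test uses one arm (about 13) or both arms of a population (about 26).

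**The concern.** The test of the primary outcome is left open until the data have been seen. Three consequences follow.

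- A check on about 13 values has little power, so most moderate departures from normality would pass unnoticed.
- The usual nonparametric partner of the paired t test, the signed-rank test, assumes that the differences are symmetric. If skewness prompts the switch, the switch leads to a test that is unreliable for the same reason.
- The choice may differ between post and follow-up, or between CP and TD. One contrast could then be reported as a mean change and another as a rank-based shift.

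At stake is the error rate of the primary result, and whether its time points can be read on one scale.

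**Working it through.** **The plan's own figures.** With dz=2.98 and two-sided alpha 0.05 (sidedness is not stated), the power of a paired t test comes from the noncentral t distribution with noncentrality dz√n and n−1 degrees of freedom. It is 0.741 at n=3 and 0.965 at n=4, so the stated n=4 is reproduced. Attrition: 17 × 0.75 = 12.75, or about 13, as stated.

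**Assumptions.** The article gives no distribution for the smoothness differences and says that no earlier sample data exist, so a range of shapes was simulated. The check is taken as Shapiro-Wilk at 5% and the fallback as the exact signed-rank test; the article names neither. The two-step rule uses the t test if the check passes and the signed-rank test if it fails. The null is zero mean change. Each shape had 20,000 runs, so the simulation standard error near 5% is √(0.05 × 0.95 / 20,000) = 0.15 percentage points.

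**Step 1: how often the check flags non-normality at n=13.** Gamma with skew 1: 18%. Laplace: 19%. t with 3 df: 24%. Lognormal (sigma 0.5): 33%. Exponential: 60%. Lognormal (sigma 1): 75%. The check misses most moderate departures and catches most severe skew. At n=26 it flags 22% to 67% of the moderate cases.

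**Step 2: false positives, nominal 5%.**

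| Differences | n | Fixed paired t | Signed-rank | Two-step |
|---|---|---|---|---|
| Normal | 13 | 4.9% | 4.8% | 5.0% |
| t, 3 df (symmetric) | 13 | 4.2% | 4.7% | 4.9% |
| Gamma, skew 1 | 13 | 6.5% | 6.4% | 6.9% |
| Lognormal 0.5 | 13 | 7.7% | 8.2% | 8.6% |
| Exponential | 13 | 9.1% | 10.3% | 10.6% |
| Lognormal 1 | 13 | 14.3% | 18.3% | 18.6% |
| Lognormal 0.5 | 26 | 6.4% | 10.6% | 10.4% |
| Exponential | 26 | 7.8% | 15.1% | 15.1% |

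A separate simulation of lognormal 0.5 / exponential gave, for two-step against fixed t, 8.9% / 10.7% against 7.6% / 8.6% at n=13, and 10.9% / 14.7% against 6.7% / 7.4% at n=26.

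**Step 3: how much is due to the switch.** From the table at n=13, lognormal 0.5: total excess 8.6 − 5 = 3.6 points, of which 7.7 − 5 = 2.7 is present with a fixed paired t test and 8.6 − 7.7 = 0.9 comes from switching. Exponential: 5.6 points in total, 4.1 with the fixed t test and 1.5 from switching. The separate simulation puts the switch at 1.3 and 2.1 points. At n=26 the balance reverses: switching adds 10.4 − 6.4 = 4.0 and 15.1 − 7.8 = 7.3 points, because the signed-rank error grows with n while the t test's falls.

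**Step 4: the same shapes compared between arms, 13 v 13.** On change scores, the two-sample t test gives 3.6% to 4.9%, the rank-sum test 4.4% to 4.5%, and the two-step rule 4.4% to 5.2%. Permuting arm labels gives 4.1% to 6.0% (3,000 runs per shape) and 4.3% to 5.3% in a separate run. For normal data and an assumed between-arm difference of 1 SD, the t test has noncentrality √(13/2) = 2.55 on 24 df and power 0.69; the permutation test also gives 0.69.

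**The case against.** The strongest reply is that the quoted sentence does little of the damage. At n=13 a fixed paired t test is already above 5% under skew, and the switch adds 1 to 2 points. In a between-arm comparison the two-step rule itself stays near 5%, so the benefit of the permutation test comes mainly from comparing arms and not from avoiding the normality check. This stands for n=13, and it shapes the fix.

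Other points also stand:

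- The harm needs skewed differences. The signed-rank test is exact when differences are symmetric about zero, which includes no change with exchangeable before and after values. Under mild skew the two-step rule reaches only about 7%.
- The signed-rank test does not target the mean, so part of its excess under a zero-mean null reflects a different estimand.
- Shapiro-Wilk and signed-rank are assumptions. Leaving the check and the fallback unnamed is detail that an article may leave to a fuller document, and it is not held against the plan.
- The trial describes itself as pilot-phase.

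Pooling arms to n=26 does not rescue the rule. Detection improves, but under skew the two-step error is higher than at n=13.

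**Conclusion.** The point holds in a limited form. The plan lets the data choose the primary test at a sample size where the choice is poorly informed. Where skewness would justify a switch, switching does not bring the error back to 5%: about 9% to 11% against about 8% to 9% for a fixed paired t test at n=13, and about 11% to 15% against about 7% at n=26, under moderate to strong skew. These figures assume Shapiro-Wilk at 5%, a signed-rank fallback and a zero-mean null.

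A reader might infer that the trial's error rate is inflated whatever the data look like. The documents do not support that: there is no inflation with normal or symmetric differences, and nothing in the article shows that smoothness changes will be skewed. Nor does the evidence show that a permutation test beats a two-step rule when both compare arms. What is shown is that the shape is unknown in advance, that the planned rule is sensitive to it, and that a between-arm test using controls the trial already randomises is not. The change should be made, and it is modest in size.

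**What to change.** For the primary outcome only, replace the paired tests and the switching sentence in both Trial Design and Statistical Methods with text such as:

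> Change in smoothness from baseline is compared between the randomised arms, separately within CP and within TD, at post-assessment and at follow-up, by a permutation test of the arm labels (permuted within blocks as allocated). The mean difference and 95% CI are reported. The test is not changed after inspecting the data. A rank-based test is a sensitivity analysis only.

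Keep the existing nonparametric provision for the exploratory secondary outcomes, where it is reasonable for the clinical scales. The sentence in Statistical Methods now covers primary and secondary outcomes together, so it needs splitting rather than deleting.

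The cost is a few sentences and a few lines of code, and the article says that the trial has not started. The p values come from resampling, so the number of permutations and the seed should be fixed. If the data prove strongly non-normal, a rank test could have more power. The sample size rationale rests on a within-subject effect, so it should say what the between-arm test can detect: at 13 v 13, power is 0.69 for a difference of 1 SD.

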### Outcomes

All participants will be assessed for outcome measures at a site using sEMG sensors embedded with inertial measurement units (ATI-Nano 25, ATI Industrial Automation, North Carolina) and the robot-force transducer unit. All assessments and measurements are noninvasive and involve minimum risk to the participants. The accelerometry data will be used to assess smoothness of movement during the execution of a prescribed movement and measures muscle activation patterns during assessments involving the robot-force transducer unit used to measure force and torque outputs within the reachable space of the upper limbs of the participant. In addition, the robot is programmed to produce a path of zero resistance, within the reachable space, that provides haptic feedback perpendicular to the path. For assessing children with CP, we will collect clinical and quantitative measures of upper limb range of motion, motor function, dystonia, and spasticity. The outcome measures will be obtained before, after the intervention, and at 1-month follow-up (Textbox 2).

Assessments 1 to 4 are standard clinical questionnaires and tests. Assessment 5 is a quantitative test of spasticity based on sEMG recordings and angle velocity of a joint by manual manipulation.

Assessment 6 involves the robot, force sensor, and sEMG. A predetermined zero-force path has been programmed by the research team to allow the robot to move through straight lines connected to 5 points on a vertical plane. These positions coincide with the 5 positions of the training intervention, resting in a reachable rhombus-like configuration. The participants will attempt to find and move along a zero-force path. The force transducer will measure the forces exerted by the participant as they do so. This task will be limited to a 7-min period or until the task is complete.

Measured outcomes. Measures for all participants (ie, listed from 6 to 10 will be done for all participants). The remaining articles are outcome measures for participants with cerebral palsy, that is, these will be specific to participants with cerebral palsy.Dyskinesia Impairment ScaleSelective Control of the Upper Extremity ScaleQuality of Upper Extremity Skills TestTardieu TestMontreal Spasticity Rating TestZero-Force Channel AssessmentSurface electromyography and accelerometryForces and torques against force sensorWorld Health Organization Disability Assessment Schedule 2 Children and YouthQualitative Feedback Module

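### Baseline smoothness is used only by subtraction: no arm comparison or covariate is stated, and an arm contrast built on the raw differences would generally be less efficient than a baseline-adjusted one

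*Protocol article*

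**What the plan says.** Choice of Comparator sets up a randomised control within each population: "The CP and TD groups will be randomly assigned to an intervention or no-intervention (control) group". It adds that "The control groups will be assessed in the same schedule as the intervention groups". Under Outcomes, "The outcome measures will be obtained before, after the intervention, and at 1-month follow-up". Baseline smoothness is therefore available in both arms.

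Statistical Methods names the test: "We will conduct paired *t* tests on movement primary and secondary outcomes for the CP and TD groups independently". It continues: "Differences before and after as well as before and follow-up will be obtained on the primary outcome measure: smoothness of movement". Trial Design says the same, and both sections fall back on nonparametric techniques if normality fails. Neither states a test of intervention against control, and no covariate, regression or analysis of covariance appears anywhere in the article.

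Sample Size rests on a within-subject effect: "effect size for within-subjects designs of dz=2.98, alpha=.05, and power=0.8 yields a required sample size of n=4 in each comparison group". It then raises the number: "Given the wide age range and motor impairment characteristics in the eligibility criteria for this study, we propose a sample size of n=17". With 25% attrition, about 13 children per group are expected to remain. Allocation describes blocked randomisation and mentions no balancing on baseline smoothness.

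**The concern.** The stated objective is to establish the effect of the training, and the design is a randomised controlled trial. That calls for a contrast between arms. The only outcome quantities the plan defines for it are the raw differences from baseline, so the natural repair would be a two-sample test on those differences.

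A change score fixes the slope on baseline at 1. When the true slope is below 1, subtraction carries part of the baseline noise into the outcome, which widens the confidence interval. It also over-corrects when the arms differ at baseline by chance: the arm that starts worse tends to show the larger improvement. With about 13 children per arm, chance differences of a noticeable size are not rare. Efficiency would then be given up although the baseline measurement that recovers it is already collected.

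**Working it through.** **1. The plan's own figures.** For a paired t test, noncentrality is dz × √n with n − 1 degrees of freedom. With dz = 2.98 and two-sided alpha 0.05, n = 3 gives 74.1% power and n = 4 gives 96.5%. The stated n = 4 is therefore reproduced. Attrition: 17 × 0.75 = 12.75, about 13. Both describe a within-child comparison, not an arm contrast.

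**2. Inputs for the arm contrast.** From the article: 13 per arm, 1:1 allocation, alpha 0.05 (taken as two-sided, which is what reproduces n = 4). Assumed: equal SDs at both visits, and a baseline-to-post correlation rho, shown over a range because the article gives none.

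**3. Variance ratio.** In units of the outcome variance:
- change score: 2(1 − rho)
- baseline-adjusted residual: 1 − rho²
- ratio: (1 − rho²) / [2(1 − rho)] = (1 + rho)/2

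Estimating the slope multiplies the adjusted variance on average by 1 + 1/(2n − 4) = 1 + 1/22 = 1.045 and leaves 2n − 3 = 23 degrees of freedom instead of 24.

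**4. Power.** The reference effect is the one for which a two-sample t test on change scores has 80% power at 13 per arm: 1.145 change-score SDs. For that effect (noncentral t):

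| rho | (1 + rho)/2 | × 1.045 | adjusted power |
|---|---|---|---|
| 0.3 | 0.65 | 0.680 | 92.4% |
| 0.5 | 0.75 | 0.784 | 88.4% |
| 0.7 | 0.85 | 0.889 | 84.3% |
| 0.8 | 0.90 | 0.941 | 82.2% |
| 0.9 | 0.95 | 0.993 | 80.1% |
| 0.95 | 0.975 | 1.019 | 79.1% |

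Simulation of 20,000 trials per value agrees (change score versus adjusted): 80.4% versus 88.9% at rho = 0.5, 80.3% versus 84.4% at 0.7, and 79.7% versus 80.0% at 0.9.

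In children: at rho = 0.5, matching 88.4% with change scores takes between 16 per arm (88.0%) and 17 per arm (89.9%), instead of 13.

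**5. At the plan's effect.** If the arm difference were 2.98 change-score SDs, the change-score test with 13 per arm would already have essentially 100% power, so adjustment would add nothing visible.

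**6. Chance imbalance.** The baseline difference between two arms of 13 has SD √(2/13) = 0.39 outcome SDs. The probability that it exceeds 0.5 SD in either direction is about 20%. Given an imbalance of that size, the change-score contrast shifts by (1 − rho) × 0.5: 0.25 SD at rho = 0.5, 0.15 at 0.7 and 0.05 at 0.9.

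**The case against.** The strongest objection is that the loss belongs to an analysis the article does not contain. The stated tests are paired within group, and between-arm covariate adjustment has no role in a paired t test. A reader might infer that the planned primary analysis itself loses power. The document does not support that. The loss applies to an arm contrast that the design and objective call for but the text never specifies. The point survives in that conditional form, because adding a two-sample test on the plan's own differences would leave the inefficiency in place.

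A reader might also infer from the described variability of dystonic movement that rho must be well below 1. The article gives no visit-to-visit reliability for the smoothness index. The wide age and impairment range raises between-child variance, which tends to push rho up and shrink the gain. The larger gains in the table therefore cannot be presented as the expected case.

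Third, chance imbalance may be read as bias. Under randomisation a change-score contrast is unbiased on average, and its standard error already reflects such imbalance. The shift is conditional on the imbalance observed, so it restates the efficiency argument and is not a second defect.

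Fourth, the 1.145 SD effect is a reference chosen for this check, and the article describes a trial in the pilot phase. No power shortfall is shown at the plan's own effect. That stands, although the plan did not rely on that effect either: it enlarged the groups from 4 to 17.

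Finally, covariates are often left to an analysis plan. That carries less weight here, because the article names the test and the handling of baseline in two sections.

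**Conclusion.** The concern holds in a limited form. The article uses baseline smoothness only by subtraction and states neither an arm comparison nor a covariate. An intervention-versus-control contrast on those differences would be valid but generally less efficient than a baseline-adjusted one.

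The size depends on an unknown rho. From a reference power of 80% at 13 per arm, the gain is about 12 points at rho = 0.3, 8 at 0.5, 4 at 0.7 and 2 at 0.8. It is nil at 0.9 and becomes a loss of about 1 point at 0.95. These figures assume equal SDs at the two visits, a linear relation to baseline and approximate normality. The change is worth making because it costs little across the whole range and also supplies the arm contrast that the objective needs.

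**What to change.** In Trial Design and Statistical Methods, specify as the primary analysis, within CP and separately within TD, a linear model of post-assessment smoothness on randomised arm with baseline smoothness as covariate. Specify the same model for 1-month smoothness. Report the adjusted arm difference with its 95% confidence interval, and keep the within-arm paired differences as descriptive.

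In Sample Size, state that the within-subject dz does not describe this arm contrast.

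The statistical cost is one degree of freedom and a linearity assumption. No extra visits, measurements or children are needed. It is more than a wording change, since it makes the arm difference the primary quantity and detaches it from the present sample-size basis. The article says the trial has not started, so the model can still be fixed in advance.
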